##### Cognitions and behaviors of healthcare professionals

Dimensions of communication and relationships among healthcare professionals (i.e. relational coordination) are measured similarly to the assessment of relational coproduction in older people and their healthcare professionals. The 7 questions of the validated measure of relational coordination assess the dimensions of communication (frequency, timeliness, accuracy, and problem-solving nature of communication) and relationships (shared knowledge, shared goals, and mutual respect) among healthcare professionals [95]. Professionals involved in healthcare delivery for frail older people (e.g. GPs) are asked to assess the quality of their communication and relationships with other professionals (e.g. elderly care physicians). As a result, we evaluate separately the connections of healthcare professionals with other types of professionals involved in the care process. Altogether these dimensions form the construct of relational coordination [76, 91–93]. We followed earlier research that also used this instrument to assess cognitions and behaviors among professionals [40, 41].

### Quality of integrated primary care for frail community-dwelling older people

#### Older patients’ experiences with integrated primary care

Quality of integrated care is measured using the short version of the Patient Assessment of Chronic Illness Care (PACIC-S) [96]. The 11-item PACIC-S measures the extent to which care is proactive, planned, and patient-centered as perceived by patients [38, 97, 98]. In addition, the instrument incorporates key components related to self-management support, e.g. goal setting, problem-solving, and follow-up [99, 100].

#### Healthcare professionals’ perceptions of integrated primary care

Quality of integrated care as perceived by healthcare professionals is assessed by means of the 21-item short version of the Assessment of Chronic Illness Care (ACIC-S) [101]. The instrument comprises six levels of system change that affect quality of healthcare delivery [102].

### Covariables

Several variables will be measured to provide insight into the characteristics of the study population and to facilitate interpretation of the outcomes of the evaluation study. Socio-demographic data (e.g. age, sex, marital status, educational level, net household income, and living situation) are collected during the interviews with frail older patients. We assess several additional variables in order to attempt to account for potential case-mix differences that may be introduced due to the non-random allocation of older patients to the intervention and control groups. Multimorbidity, physical functioning, cognitive functioning, and social functioning are assessed. Morbidity is assessed by indicating morbidities experienced in the past 12 months from a predefined list of 17 conditions (e.g. diabetes, chronic obstructive pulmonary disease (COPD), osteoporosis, and cancer). Multimorbidity is defined as the presence of two or more conditions from this list [103]. Physical functioning is assessed by means of a modified version of the Katz Activities of Daily Living index (Katz ADL index). Functional limitations are assessed for 8 activities in daily life, i.e. bathing, dressing, toileting, eating, continence, transfer, walking, shaving or to comb one’s hair [104, 105]. Additionally, cognitive functioning is assessed by means of the 12-item Mini-Mental State Examination (MMSE-12). The MMSE-12 focuses on cognitive aspects of mental functions and includes elements like orientation to time and place, recall of words, and complex commands, e.g. drawing a figure [106, 107]. Social functioning is assessed by means of the social component of the Dutch version of the 20-item Short Form Health Survey (SF-20) [108–110]. Next to the additional variables that are measured at the level of the older adults, we collect socio-demographic data of healthcare professionals (e.g. age, sex, educational level, occupation, and working hours).

### Process evaluation

An integral part of the evaluation of the FFF approach to determine the quality of integrated care and to understand underlying mechanisms explaining effectiveness is the process evaluation. A process evaluation is useful because of the complexity of the integrated care approach, which comprises multiple elements and affects various outcomes [111]. These elements may be mutually reinforcing and have a synergistic effect [112]. Also, GP practices differ with respect to important characteristics. Oakley and colleagues [113] state that approaches may be implemented and received differently across sites. According to Øvretveit and Gustafson [112], effectiveness of integrated care approaches often depends on the degree of implementation. Assessment of the implementation and context is therefore essential and may help to gain insight in how processes work to produce effects. Thus, it is important to describe the multicomponent approach, its implementation and context, and discover the factors that are crucial for the implementation and outcomes [112]. Therefore, the aim of the process evaluation is to provide a thorough description of the FFF approach, assess the implementation and the context of this integrated care approach, and to provide factors and conditions that are critical for success. This also applies to the control practices. They will be studied in-depth and usual care delivery will be richly described. The process evaluation study identifies whether the FFF approach contributes to integrated care delivery in order to effectively support independently living older persons. We aim to enhance our understanding of the challenges faced by healthcare organizations and professionals and identify factors that facilitate or hinder the implementation of integrated care in a primary care setting. Therefore, in addition to the quantitative data described in the previous section, also qualitative data are gathered from actors at all levels, including frail older persons, healthcare professionals involved in the care process, and professionals involved in the management of healthcare delivery. A combination of quantitative and qualitative data will provide a richer understanding of the effects and processes of integrated primary care for frail older people.

Process indicators are registered continually during the follow-up period of 12 months. Descriptions of patient visits by practice nurses and geriatric nurses, medication reviews, assessment outcomes, and individualized care plans describing the provided self-management support are analyzed. Data are collected from data registries (e.g. information systems). We collect data on several process indicators that are specifically related to the FFF approach. Examples are the number of frail older patients that are discussed in multidisciplinary consultations, the number of older adults that have an individualized care plan, and the number of multidisciplinary consultations per year. Moreover, field notes are made at several multidisciplinary consultations executed by intervention GP practices and general meetings related to the FFF approach. Examples are educational meetings for geriatric nurses and practice nurses, steering committees, and working groups. Furthermore, semi-structured face-to-face interviews are conducted with a sample of healthcare professionals involved in the care process for frail independently living older patients. We aim to interview a diverse group of professionals, including practice nurses, elderly care physicians, and case managers. Hence a purposeful sampling procedure will be used, which can be used in qualitative research to collect data from the participants who are knowledgeable about the topic [114, 115]. Healthcare professionals are encouraged to describe and reflect on their experiences with healthcare delivery for frail older patients living in the community. In addition, several professionals involved in the management of healthcare delivery are interviewed. Examples are the project manager of the FFF approach and policy advisors of different healthcare organizations (e.g. homecare agencies). Also, semi-structured face-to-face interviews are held with a sample of independently living frail older persons. The aim is to gather the reflections on experiences of patients with the FFF approach (intervention group) or care as usual (control group) from their own perspective. To create a diverse sample of older people, we aim to select participants with different characteristics. Besides these semi-structured interviews, face-to-face interviews based on a more structured interview template are held with GPs of all participating GP practices as well. As the GP has the lead in the implementation and execution of the FFF integrated care approach, we decided to interview GPs to assess exactly how care is being delivered in the different intervention GP practices. We also assess how care for community-dwelling older people is being delivered in the control GP practices (care as usual). We developed an interview template based on the Chronic Care Model (CCM) [38, 97]. The CCM highlights system changes in several areas (e.g. decision support and clinical information systems) to guide quality improvements [38, 97]. Important interventions related to care delivery are classified according to the areas of system change in the interview format. Examples of interventions are the systematic follow-up of patients and the use of clinical guidelines. Data about the implementation of these various interventions within each of the areas of system redesign are collected. Altogether an extensive description of (un)successfully implemented interventions is provided. Interviews are recorded with permission of the GPs and finalized data are send back for member checking and corrections.

### Qualitative analyses

All interviews are audio-taped with permission of the patient or professional. After the transcription of the audio-taped interviews, latent content analysis is used [116, 117] in which the focus is primarily on analyzing the underlying meaning of the content [118, 119]. The Dutch texts derived from the interviews will be translated into English. All texts will be read several times by researchers with expertise in qualitative research to ensure a holistic understanding. We will extract, code, and categorize meaning units. Underlying meanings of categories will be expressed in themes [116].

### Integration of qualitative and quantitative data

An embedded mixed methods design is used where qualitative data is added to the quasi-experimental design. During the study both quantitative and qualitative data will be collected and analyzed. For example, qualitative data will be collected during the study to explore how participants experience the FFF approach. By using this embedded design the qualitative data augment the (cost)effectiveness study, which is a popular approach within implementation and dissemination research similar to the FFF approach [120, 121]. We will also use an explanatory design in which qualitative data helps to understand quantitative results [115]. We will for example collect and analyze quantitative data with regard to the quality of (integrated) care as perceived by healthcare professionals. Subsequently, these results will be followed up with in-depth qualitative data to explain and expand the quantitative results (e.g. unexpected results, significant differences between the groups in perceived quality of care).

### Economic evaluation

The healthcare expenditures have increased substantially in the previous decades [122]. Moreover, an increase in healthcare costs associated with aging is expected [123]. In response to these increases, challenges with respect to allocating scarce healthcare resources over interventions become apparent [124, 125]. The decision to fund and implement one intervention over another will not only have an effect on patient outcomes, but also on (publicly funded) healthcare resources and resources outside healthcare. Accordingly, consideration of effects as well as costs is important in informing decisions related to the optimal resource allocation and reimbursement of healthcare approaches. Such decisions require evaluations that go beyond assessing merely effectiveness and processes of healthcare approaches, and should include an economic evaluation as well [125].

The primary aim of our economic evaluation is to determine whether the FFF approach is cost-effective when compared to care as usual for frail community-dwelling older persons. We comparatively assess the costs and effects of the FFF integrated primary care approach and care as usual. The economic evaluation is performed from the societal perspective which implies that, in principle, all relevant costs and effects are incorporated in the analysis [125, 126]. Our economic evaluation comprises a cost-utility analysis and a cost-effectiveness analysis.

For the cost-utility analysis, the effectiveness is measured using quality-adjusted life-years (QALYs). QALYs are a preference-based health measure that comprises length and health-related quality of life [127]. For the measurement of an older person’s health-related quality of life, we use the EuroQol (EQ-5D-3L) health-related quality of life instrument that covers 5 health dimensions: mobility, self-care, usual activities, pain and discomfort, and anxiety and depression. Scores on a three-point scale indicate the older person’s level of functioning: no problems (1), some or moderate problems (2) or severe problems (3) [128, 129]. Utility scores are calculated by means of the Dutch tariff [130]. The utility scores are used to calculate QALYs gained or lost during the follow-up period of the study by applying the area-under-the-curve method [131, 132]. Estimating QALYs allows the comparison of our outcomes with the cost-effectiveness of other integrated primary care approaches [133].

In economic evaluations of healthcare approaches that are aimed at improving well-being, it is recommended to use well-being instruments alongside the more conventional health-related quality of life instruments [134]. QALYs focus mainly on health and to a lesser degree on well-being in general [135]. With respect to evaluating primary care approaches aimed at frail older people, it is crucial to have outcome measures that also go beyond health and evaluate a wider range of benefits for older people [136]. Due to the lack of preference scores or utilities for well-being, a cost-effectiveness analysis is conducted with incremental effectiveness expressed as the difference in mean SPF-IL scores. Scores on the four-point scale of the multidimensional SPF-IL instrument range from never (1) to always (4). Higher mean scores indicate a greater well-being [34]. Both the SPF-IL and the EuroQol (EQ-5D-3L) are completed by frail older patients at baseline (T0) and 12 month follow-up (T1).

Intervention costs, healthcare costs, and patient-related costs are considered relevant for the economic evaluation. *Intervention costs* consist of all costs that can be attributed to the delivery of the FFF approach, excluding the research-specific costs (e.g. executing the interviews with older patients and professionals). Examples are costs that are associated with the proactive case finding of frail elderly in the community and multidisciplinary consultations in GP practices. We assess the average amount of time for each of the activities related to the FFF approach using time registrations of healthcare professionals and by registering time during observations. *Healthcare costs* relate to (telephone) consultations with GPs and practice nurses, emergency GP, admissions to hospitals, nursing homes or homes for the elderly, homecare services, day care, nursing care, visits to paramedics, psychosocial care, and prescribed medications. Only consultations that are not already part of the FFF integrated care approach are included. Healthcare utilization is assessed by means of extracting data from electronic health records within GP practices and homecare organizations. Moreover, health service use is measured by asking older adults directly about their healthcare use during the interview (see paragraph ‘Data collection and informed consent for the evaluation study’). Patients indicate at baseline (T0) and 12 month follow-up (T1) what type of care they received and how often (e.g. hours of homecare or days of hospitalization). *Patient-related costs* include costs that are covered by frail older people themselves, like purchasing assistive aids (e.g. wheeled walkers) or time investments related to the FFF approach. This data is collected during the interviews with older persons.

For the valuation of the healthcare costs, the latest version of the Dutch manual for costing in healthcare is used [133]. We multiply volumes of resource use (e.g. days in hospital) with standardized costs per unit of resource use (in euros) to estimate costs of each approach (i.e. FFF approach and care as usual). When these standardized costs per unit of resource use are not available, costs are estimated using true economic costs, average reimbursement fees or literature.

The economic evaluation includes calculations of the cost-effectiveness and cost-utility ratios. For comparing the costs and effectiveness of the FFF approach and usual care, incremental cost-effectiveness ratios are calculated (ICERs). In this way, the additional costs and effects of the FFF approach compared with usual care are determined. The ICER in the cost-effectiveness analysis represents the incremental costs per point improvement in well-being (SPF-IL score). The ICER in the cost-utility analysis expresses the incremental costs per QALY gained. In the ratio, the numerator includes the difference in costs and the denominator the difference in effects [124]. Sensitivity analysis is performed to assess the robustness of a series of predefined assumptions. A cost-effectiveness plane and an acceptability curve are added.

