### Study design

The longitudinal evaluation study has a mixed methods design in which a combination of quantitative and qualitative research methods are employed in order to evaluate the effectiveness, processes, and cost-effectiveness of the FFF approach. The evaluation study is performed between 2014 and 2017. The study has a matched quasi-experimental design with one pretest and one posttest measurement, i.e. the effects are measured before and after the intervention. Measurements are performed at baseline (T0) and 12 months thereafter (T1). Moreover, the study includes an intervention and a control group (i.e. intervention and control GP practices).

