***Step 3:*** GPs of the intervention group make their own selection of eligible patients to be included in the FFF approach. This selection can be based on the frailty scores obtained by the administration of the self-report TFI questionnaire but can also be based on additional interviews and measures that are performed by the healthcare professional as part of the care provision. Although the TFI is a reliable and valid instrument for measuring frailty in community-living older adults [82, 88], the previously stated added value of other interviews and measures to assess frailty underlines the importance of not relying solely on the TFI as a measure to identify frail older patients [83]. Consequently, patients that are not frail according to the TFI (score ≤ 4) but are considered frail based on other examinations performed by healthcare professionals may nevertheless be selected for the FFF approach.

***Step 4:*** Eligibility of the frail older people selected in Step 3 is then assessed in terms of the inclusion and exclusion criteria by the researchers. For participation in the evaluation study we exclude (1) older people living in nursing homes or homes for the elderly, (2) persons having an estimated life expectancy of less than 3 months, and (3) people with an inadequate understanding of the Dutch language. A challenge in quasi-experimental designs is to reduce the risk of selection bias, i.e. preexisting differences in characteristics between the intervention group and control group due to the absence of random intervention assignment. This may result in a biased posttest measurement. In order to acquire unbiased estimates of the effects, the most important covariables should be balanced between intervention and control groups [89, 90]. To increase comparability of the intervention and control groups, we use one-to-one matching: each individual participant in the intervention group is matched to one participant in the control group with the same values of the key covariables, namely sex (male or female), frailty score (score on the TFI), and educational level (high or low). This one-to-one matching is performed by the researchers.

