The proposed evaluation study has potential limitations and challenges. First, the absence of randomization makes the design more susceptible to bias [139]. Especially selection bias is a major concern in non-randomized studies. Systematic differences between the groups result in incomparable groups which ultimately may lead to biased estimates of the intervention effect [140]. To reduce the impact of this bias on the outcome measures studied, we aim to control for important factors in the analysis of the data and by means of matching [141]. To ensure that the intervention and control groups are similar for key covariables, we use one-to-one matching to balance groups instead of matching on a higher level (at healthcare practice level). Moreover, when necessary we use case-mix adjustments to take into account important dissimilarities. However, it is stated by Deeks and colleagues [140] that the degree to which techniques can sufficiently adjust for differences between the groups is still unclear, which ultimately provides no guarantee for unbiased study results [140]. In addition, unknown and unmeasured factors can still influence the outcome [142]. Second, the design of the study makes it impossible to blind participating healthcare professionals and frail older patients. Knowledge of the status of the person (receiving either the FFF approach or care as usual) may have an influence on the responses and may affect compliance [143]. Nevertheless, the interviewers that conduct the interviews with frail older persons are kept unaware of the group the person is in (intervention or control GP practice), so that the interviewers collecting outcome data are not influenced by that knowledge. Blinding of the interviewers aids to reduce differential outcome measurements (information bias) [143]. Due to the nature of the evaluation study, however, it is possible that the patient inadvertently reveals his or her status during the interview (e.g. disclosing information that is specific to the FFF approach). Third, one of the core challenges of the evaluation study is the willingness of frail community-dwelling older patients to participate in the study, especially in the long-term. Recruitment of appropriate numbers of patients requires a sufficiently long period [144]. We aim to optimize participation in the evaluation study by means of home visits instead of interviews over the telephone, recruiting interviewers that live in the same region as the older adults, and sending letters to older patients on behalf of their own GP. Fourth, although control GP practices continue to provide usual care, GPs in the control group may start initiatives to improve care delivery for frail older patients. We collect data on various interventions that are implemented to improve care for older adults and we monitor and describe the activities performed by the GPs. In contrast to the intervention GP practices, control practices are not supported financially by the health insurers to implement elements of the FFF approach. Fifth, recall bias may potentially affect our study findings. Earlier research using a 12 months period of asking patients about their healthcare visits show both under-reporting and over-reporting effects [145]. Administrative data could be included to accurately capture resources for an economic evaluation (if filled in correctly). Sixth, while we included patients and professionals in our theoretical framework and study protocol we did not include informal caregivers. Given their important role in supporting community-dwelling frail older people they are expected to influence the well-being of older persons as well. Given the complexity of the theoretical framework as presented in this paper we decided to first unravel the underlying mechanisms in the relationship between quality of care, cognitions and behaviors of patients and professionals and older persons’ well-being. Future research should look at the role of informal caregivers and their cognitions and behaviors as well. It may be easier to improve outcomes if the patient’s partner is a good self-manager with a positive frame of mind compared to a partner who is depressed, has low self-efficacy and poor investment behavior.

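### The economic evaluation is called societal but its cost categories leave out informal care; its incremental costs and effects are also not tied to the adjusted effect analysis

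*Protocol article*

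**What the plan says.** All places are in the protocol article.

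**Perspective and costs.** The Economic evaluation section states: "The economic evaluation is performed from the societal perspective which implies that, in principle, all relevant costs and effects are incorporated". A little later it says: "Intervention costs, healthcare costs, and patient-related costs are considered relevant for the economic evaluation". It describes the patient-related category as what the older people pay or invest themselves, with assistive aids and their own time for FFF as examples. Informal care is not named. In Strengths and limitations the authors write that "we did not include informal caregivers" and explain this by the complexity of the theoretical framework.

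**Effects and ratio.** The cost-effectiveness analysis has "incremental effectiveness expressed as the difference in mean SPF-IL scores". QALYs come from EQ-5D utilities at T0 and T1 by the area-under-the-curve method. The ICER is described thus: "In the ratio, the numerator includes the difference in costs and the denominator the difference in effects".

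**Bias control elsewhere.** Study design says: "The study has a matched quasi-experimental design with one pretest and one posttest measurement". Matching is on sex, TFI score and educational level. Statistical analyses provides a multilevel model and a difference-in-differences model for the effects at 12 months, says that confounding is accounted for, and allows baseline adjustment where needed.

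**The concern.** A societal ratio is meant to capture a shift of burden between payers and families. The article itself makes such a shift plausible. The Background says that policy expects frail older people to arrange informal care and restricts access to long-term care. Strengths and limitations calls caregivers' role important. The Medication review component may involve informal caregivers or relatives directly. If FFF reduced formal home care because relatives did more, the plan would book a saving with no offset. If FFF relieved relatives, the plan would miss a benefit. Either way, a reader using the result for reimbursement would take the label at its word.

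The second issue is whether the incremental effects and costs receive the same protection against non-random allocation as the effect analysis. Costs and QALYs appear only in the Economic evaluation section, and that section names no adjustment.

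**Working it through.** The plan gives no ICER, cost or utility figure, so there is nothing of its own to reproduce on this point. Part A is a comparison of text. Part B is arithmetic on stated assumptions.

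**A. Does caregiver time fit a listed category?**
- Intervention costs: those attributable to delivering FFF, timed from professionals' registrations and from observations. A relative's hours of care are not part of this.
- Healthcare costs: GP and nurse contacts, admissions, home care, day care, paramedical and psychosocial care, medication. All are formal services.
- Patient-related costs: what the older people bear themselves. Care given by a relative is borne by the relative.

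The three categories leave unpaid care out, while the perspective sentence claims that in principle nothing relevant is left out. The documents give neither caregiver hours nor a price. As a pure assumption, at EUR 10 to 15 per hour a change of one hour per week is 52 × 10 = EUR 520 to 52 × 15 = EUR 780 per patient-year. The sign is unknown.

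**B. What could an unadjusted difference do?**

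Inputs from Sample size: SD 0.45 and a target of 1/4 SD, so the planned effect is 0.45 / 4 = 0.1125 points. Assumptions, not in the documents: a baseline gap g that remains after matching, and a pre-post correlation r of 0.5 to 0.7 as the share of the gap still present at T1.

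1. SPF-IL. The unadjusted T1 difference is the true effect + r × g. For g = 0.1 SD, the carry-over is 0.05 to 0.07 SD. Divided by 0.25 SD, that is 20% to 28% of the planned effect.
2. In points, g = 0.1 × 0.45 = 0.045, and the carry-over is 0.0225 to 0.0315. With the gap against FFF, the observed difference falls to 0.0900 or 0.0810. At a fixed cost difference the ICER is then 0.1125/0.0900 = 1.25 to 0.1125/0.0810 = 1.39 times its true value. With the gap in favour of FFF, the difference is 0.1350 or 0.1440, and the factor is 0.83 to 0.78.
3. QALYs. With two measurements one year apart, QALY = (u0 + u1)/2. A baseline utility gap g adds g/2 through u0 and r × g/2 through u1, together g(1 + r)/2. This is at least g/2 for any r of zero or more, and 0.75g to 0.85g for r of 0.5 to 0.7. For an assumed g of 0.01 to 0.05 the result is 0.0075 to 0.0425 QALY.
4. Limit of the illustration. Under the same carry-over model a difference-in-differences estimate shifts by r × g − g = −(1 − r)g, which is −0.03 to −0.05 SD for g = 0.1 SD. It is free of the gap only if the gap would have persisted unchanged. The figures therefore show that the choice of estimator matters, not that one choice is bias-free.

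Matching does not settle this, because baseline SPF-IL, utility and prior care use are not matching variables. Intervention GPs may also select patients on clinical examination beyond the TFI, and no such judgement is described for the controls.

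**The case against.** **On costs.** The perspective sentence is qualified by the words in principle, the examples of patient-related costs are open-ended, and the exclusion of caregivers is disclosed with a reason. These points soften the conflict but do not remove it. The category is still defined by who bears the cost. The reason given concerns the theoretical model, not costing, and nowhere is the economic perspective narrowed to match.

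**On effects.** A reader might infer that the plan divides raw group differences, that the ICERs will be confounded, and that the trial will report two different effects on well-being. The text does not support this. The phrase on mean SPF-IL scores names the unit of effect, not the estimator, and fits an adjusted contrast equally well. The sentence on numerator and denominator is the standard definition of an ICER. The section also speaks of cost per point of improvement, which may mean change. Statistical analyses promises difference-in-differences, attention to confounding and baseline adjustment where necessary, and does not exclude the economic outcomes. An area-under-the-curve QALY can be regression-adjusted, and a condensed article may leave such detail to a fuller plan. All of this stands. What remains is that the one section defining the ICER inputs does not connect them to those methods.

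**Conclusion.** The main point holds: the societal label and the stated cost categories contradict each other on informal care and must be reconciled. It rests on the wording alone. Its monetary size cannot be established from the documents, and the euro range is illustrative.

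The secondary point holds only conditionally: if unadjusted differences were used, the ICERs could be confounded. The only result that needs no assumed figure is that a two-point QALY difference carries at least half of a baseline utility gap that does not reverse. The 20% to 28% for SPF-IL depends on an assumed 0.1 SD gap and an assumed correlation of 0.5 to 0.7. Neither point affects the primary effect analysis. Both concern one of the study's three stated aims and should be corrected.

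**What to change.** 1. **Perspective.** Either add hours of informal care per week to the care-use questions already asked at T0 and T1, and state how they are valued, or restate the perspective as healthcare and patient costs and limit the conclusion to that. The first costs one interview item and a valuation rule. The second costs a phrase and a narrower claim, and is the simpler choice if T0 interviews are already complete.
2. **ICER inputs.** State that incremental SPF-IL is taken from the difference-in-differences model in Statistical analyses, so that the ICER and the effect analysis use one estimate. State that incremental QALYs and costs come from multilevel models adjusted for baseline utility and for baseline care use or costs. Build the ICERs, the cost-effectiveness plane and the acceptability curve on these estimates. This costs only wording, because SPF-IL, EQ-5D and care use are already collected at T0.
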